### 3.6. Participant Evaluation

The evaluation of participants will occur at two distinct time points:

Baseline Evaluation (T0): Conducted immediately after recruitment and prior to randomization. This stage ensures the documentation of all sociodemographic and clinical variables, alongside the administration of objective cognitive tests, without the influence of group assignment.

Post-Intervention Evaluation (T1): Scheduled upon the culmination of the four-month intervention period for all groups.

Following the baseline evaluation, participants will undergo randomization to their assigned intervention arm (ALMA, Cognitive Training, or Health Education).

For a comprehensive overview of the pertinent data, please refer to the table provided in Supplementary Material S2. Table follows the SPIRIT participant timeline structure and reflects the protocol schedule described in the manuscript.

### 3.7. Data Management and Confidentiality

#### 3.7.1. Data Collection, Storage and Confidentiality

To ensure the protection of personal data and maintain participant privacy, a pseudonymization process will be implemented. Upon enrolment, each participant will be assigned a unique alphanumeric study code, which will be used for all research-related documentation, assessment forms, intervention records, and electronic databases. Directly identifiable information will not be included in the analysis dataset.

Data will be collected and managed using REDCap or an equivalent secure institutional electronic data capture platform. Access to the database will be restricted to authorized members of the research team through individual user credentials. The file linking participant identities with study codes will be stored separately from the main research database in an encrypted file accessible only to the Principal Investigator.

Study data will be stored on secure institutional servers or approved institutional platforms with restricted access. All procedures will comply with Regulation (EU) 2016/679, the General Data Protection Regulation, and Spanish Organic Law 3/2018 on the Protection of Personal Data and Guarantee of Digital Rights. No directly identifiable participant information will be included in publications, presentations, reports, or shared datasets.

#### 3.7.2. Data Quality Control, Backup, and Change Management

Data quality will be monitored throughout the study by the Principal Investigator and authorized members of the research team. The electronic database will include predefined variable labels, coding rules, range checks, and validation procedures whenever possible to reduce data entry errors.

The database will be reviewed periodically to identify missing values, out-of-range responses, inconsistent entries, duplicate records, and discrepancies between source documents and electronic records. When inconsistencies are detected, they will be checked against the original study documentation and corrected only by authorized personnel.

Any modification made after initial data entry will be documented, including the date of the change, the person responsible, the original value, the corrected value, and the reason for the modification, where technically feasible. These procedures will allow traceability of changes and support data integrity.

Regular backup procedures will be implemented according to institutional data security policies. Before statistical analysis, the dataset will be reviewed for completeness, internal consistency, and plausibility. A final pseudonymized dataset will be created for analysis, with direct identifiers removed. Any data cleaning decisions, exclusions, or transformations will be documented in a data management log to ensure transparency and reproducibility.

### 3.8. Intervention Fidelity and Reproducibility Protocols

To ensure clinical reproducibility and strict intervention fidelity across current and future cohorts, the dynamic adaptability of the ALMA intervention follows a rigorous, manualized framework of standardized flexibility. While tasks are adaptively calibrated to address patients’ subjective complaints, these modifications are strictly constrained by a pre-established algorithmic matrix that governs task complexity (e.g., pre-defined adjustments in stimulus exposure time, working memory load, or cognitive interference layers). The structural architecture of the sessions including duration, multi-domain cognitive goals, and metacognitive training modules remains strictly invariant across all participants. Intervention fidelity will be systematically monitored using a session-by-session compliance checklist that tracks adherence to manualized timelines, objective delivery, and applied difficulty parameters.

### 3.9. Statistical Analysis

All analyses will be conducted according to the intention-to-treat (ITT) principle, including all randomized participants in the groups to which they were originally allocated, regardless of adherence to the intervention, thereby ensuring that the primary effectiveness analysis remains fully powered even if a significant proportion of participants fail to meet compliance thresholds. A secondary per-protocol analysis may be conducted including participants who complete the post-intervention assessment and, in the intervention arms, meet the predefined adherence criteria (≥70% attendance). In the event that a large majority of participants fail to reach this updated 70% attendance threshold due to severe treatment-related toxicity, a secondary sensitivity dose–response analysis will be implemented, modeling session attendance as a continuous covariate to evaluate the threshold-independent impact of intervention volume on neurocognitive outcomes.

Descriptive statistics will be used to summarize baseline sociodemographic and clinical characteristics by study arm. Continuous variables will be presented as means and standard deviations or medians and interquartile ranges, depending on their distribution. Categorical variables will be presented as frequencies and percentages. Baseline comparability between groups will be described, but statistical testing of baseline differences will not be used to determine participant inclusion or exclusion from the analysis.

The primary effectiveness analysis will evaluate change in Montreal Cognitive Assessment (MoCA) total score from baseline (T0) to post-intervention assessment (T1). Linear mixed models (LMM) will be constructed using a Restricted Maximum Likelihood (REML) estimation approach. The model will include fixed effects for group, time, and the Group × Time interaction term, and a parsimonious random-effects structure restricted to a random intercept for each participant to account for within-subject correlation across time while excluding random slopes. The Group × Time interaction will be the main parameter of interest. Both unadjusted and adjusted models will be calculated to verify the robustness of the intervention effect.

The planned between-group comparisons for the primary outcome will focus on the ALMA group intervention (G2). The first planned comparison will evaluate the difference in change in MoCA total score from T0 to T1 between G2 and the health education control group (G0). The second planned comparison will evaluate the difference in change in MoCA total score from T0 to T1 between G2 and the individual cognitive training group (G1), in order to assess the potential added value of the multidimensional group-based ALMA intervention over individual cognitive training. The comparison between G1 and G0 will not be considered a planned efficacy comparison and, if reported, will be interpreted as exploratory.

To strictly prevent statistical overfitting and safeguard the degrees of freedom given the target sample size of 21 participants per study arm, the adjusted model will be parsimoniously restricted. Specifically, a maximum of two pre-specified baseline covariates will be simultaneously controlled for as fixed effects: chronological age (in years) and educational level (in years of formal schooling). Baseline cognitive stratification variables will be excluded from the model as covariates, given that their equilibrium across groups is already mathematically guaranteed by the stratified block randomization procedure (Section 2.5). Additional clinical and psychological variables including disease stage, treatment modality, time since diagnosis, cancer-related fatigue/performance status, baseline anxiety symptoms (Hamilton Anxiety Scale), and baseline ECOG Performance Status will be exclusively examined in exploratory or sensitivity analyses rather than included simultaneously in the primary adjusted model.

Because two planned comparisons will be conducted for the primary outcome, namely G2 versus G0 and G2 versus G1, Holm–Bonferroni correction will be applied to these two comparisons to control the family-wise error rate. Holm–Bonferroni correction will also be applied to secondary outcome comparisons within each outcome family when appropriate. Any additional post hoc analyses, including G1 versus G0 comparisons, will be clearly labelled as exploratory.

Secondary outcomes will be analyzed using the same modelling framework, with each outcome assessed separately. These outcomes will include perceived cognitive function, everyday cognition, functional autonomy, anxiety symptoms, sleep quality, performance status, and everyday memory failures. For each secondary outcome, the Group × Time interaction will be used to estimate whether change from T0 to T1 differs between study arms. The planned secondary comparisons will focus on G2 versus G0 and G2 versus G1. To account for potential variations in participant insight, changes in subjective memory failures will be systematically triangulated and interpreted alongside the objective primary cognitive trajectories (MoCA scores).

Missing outcome data will be examined descriptively. The primary linear mixed model analysis will assume that data are missing at random. Patterns of missing data will be explored by comparing participants with complete and incomplete outcome data. Sensitivity analyses will include complete-case analyses and, if attrition exceeds 15%, multiple imputation by chained equations. Model assumptions will be assessed by inspecting residual distributions and model diagnostics.

All statistical tests will be two-tailed. Statistical significance for the primary analysis will be set at *p* < 0.05 after Holm–Bonferroni correction for the two planned primary comparisons. Effect estimates will be reported with 95% confidence intervals. Analyses will be conducted using IBM SPSS Statistics version 28.0.1 or equivalent statistical software.

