### 2.4. Sample Size

The planned sample size for this trial is 63 women with breast cancer undergoing active oncological treatment, with 21 participants allocated to each of the three study arms: health education control group (G0), individual cognitive training group (G1), and ALMA group intervention (G2).

The sample size calculation was based on the primary outcome, defined as the change in objective global cognitive performance from baseline (T0) to post-intervention (T1), assessed using the Montreal Cognitive Assessment (MoCA). As no directly comparable previous trial evaluating the ALMA intervention in women with breast cancer was available, the expected effect was estimated using an indirect reference study that evaluated a multicomponent cognitive stimulation programme and reported a mean post-intervention increase of 2.95 points in MoCA score [27]. Assuming a common standard deviation of 3.48, this corresponded to an estimated standardized effect size of Cohen’s d ≈ 0.85.

For the purposes of sample size estimation, this effect was converted to an approximate ANOVA effect size of f ≈ 0.40. The calculation was performed using G*Power software, version 3.1.9.7 [28], for a balanced one-way fixed-effects ANOVA with three independent groups, an alpha level of 0.05, statistical power of 80%, and equal allocation across groups. Under these assumptions, a minimum total sample of 57 participants was required to detect an overall between-group difference.

To account for an anticipated attrition rate of approximately 10%, the recruitment target was increased to 63 participants, corresponding to 21 participants per study arm. This inflation is intended to preserve statistical power for the primary analysis under the intention-to-treat principle.

Although the primary effectiveness analysis will be conducted using linear mixed models to evaluate the Group × Time interaction across baseline and post-intervention assessments, the ANOVA-based sample size calculation was used as a conservative and transparent approximation for planning purposes. Linear mixed models are expected to make efficient use of repeated-measures data and to accommodate missing outcome data under the missing-at-random assumption. Therefore, the ANOVA-based calculation was considered appropriate for estimating the minimum feasible sample size while maintaining consistency with the planned three-arm randomized design.

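### Intention-to-treat analysis does not keep the trial fully powered when attendance is poor: it keeps the headcount, not the effect size, and the sample size allows only for attrition

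*Protocol article*

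**What the plan says.** The opening paragraph of Section 3.9 (Statistical Analysis) sets the ITT population as all randomized women in their allocated groups whatever their adherence. It then draws a consequence for power: "ensuring that the primary effectiveness analysis remains fully powered even if a significant proportion of participants fail to meet compliance thresholds". The threshold, set in Sections 2.6.3 and 2.8, is attendance at 22 of 32 sessions (70%) for each woman. The same paragraph of Section 3.9 offers an optional per-protocol analysis. It also plans a dose–response analysis in case a large majority miss the threshold because of treatment toxicity.

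Section 2.4 (Sample Size) takes its effect from a reference study that "reported a mean post-intervention increase of 2.95 points in MoCA score". It continues: "Assuming a common standard deviation of 3.48, this corresponded to an estimated standardized effect size of Cohen’s d ≈ 0.85". The calculation is "for a balanced one-way fixed-effects ANOVA with three independent groups", with "an alpha level of 0.05, statistical power of 80%, and equal allocation across groups", and gives 57 women. The only allowance on top is for attrition: "To account for an anticipated attrition rate of approximately 10%, the recruitment target was increased to 63 participants". Of this allowance it says: "This inflation is intended to preserve statistical power for the primary analysis under the intention-to-treat principle".

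Section 2.9 asks women who stop the intervention to complete the final assessment all the same, so that they enter the ITT analysis. Section 6 (Limitations) acknowledges a possible loss of power, but from attrition only.

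**The concern.** Attrition and non-adherence cost power in different ways. Attrition removes T1 scores and so reduces the number analysed; enrolling more women offsets it. Non-adherence leaves the number unchanged and shrinks the mean difference, because the G2 mean becomes an average over women who had most of ALMA and women who had less of it. ITT analysis protects against the first only to the extent that T1 is obtained, and does nothing about the second.

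The sentence in Section 3.9 therefore claims a property that the design does not have. It is a positive statement in the current text, not a detail left to a separate analysis plan. What is at stake is interpretation: if attendance is poor and the ITT comparison is null, the protocol could be cited as saying in advance that the comparison was fully powered.

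**Working it through.** **Inputs from Section 2.4:** mean effect 2.95 MoCA points; SD 3.48; three equal groups; alpha 0.05; target power 80%; f ≈ 0.40; minimum N 57; recruitment target 63. Section 3.9 adds: "All statistical tests will be two-tailed".

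**Inputs that the documents do not give (assumptions):** the share of women who are adherent (p), and the fraction of the full effect that non-adherent women keep (r). I take p = 0.70 and vary r. This p is illustrative and is not derived from the attendance threshold.

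**Step 1. Reproduce the plan's figure.**

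- d = 2.95 / 3.48 = 0.848.
- Omnibus power is P(F′ > F crit), with F′ non-central F on 2 and N − 3 df and λ = N·f².
- With f = d/2 = 0.424: at N = 57, λ = 57 × 0.424² = 10.25 and power is 80.2%. At N = 54 it is 77.8%. The minimum for equal groups is 57, as stated.
- With the printed f = 0.40: power is 75.2% at N = 57 and 79.8% at N = 63 (λ = 10.08), and the minimum N is 66. This f is what follows if only G2 differs: d·√2/3 = 0.848 × 1.414 / 3 = 0.400.
- Inflation: 57 / 0.9 = 63.3 and 57 × 1.1 = 62.7, so 63 corresponds to about 10% attrition and leaves nothing for dilution.

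Both values of f are carried forward. The gap between them is a separate matter and does not drive this point.

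**Step 2. Dilute the effect.** The ITT mean effect in G2 is 2.95 × [p + (1 − p)·r]. If only G2 differs, f shrinks by the same factor. With p = 0.70, f = 0.40 and N = 63:

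| Effect kept by non-adherers (r) | Factor | Mean effect (points) | f | λ | Omnibus power |
|---|---|---|---|---|---|
| No dilution | 1.000 | 2.95 | 0.400 | 10.08 | 79.8% |
| Three quarters | 0.925 | 2.73 | 0.370 | 8.62 | 72.9% |
| Half | 0.850 | 2.51 | 0.340 | 7.28 | 65.0% |
| One quarter | 0.775 | 2.29 | 0.310 | 6.05 | 56.5% |
| None | 0.700 | 2.07 | 0.280 | 4.94 | 47.8% |

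**Step 3. Repeat with the f that reproduces 57** (f = 0.424, r = 0, so f = 0.297). At N = 57 power goes from 80.2% to 48.2%; at N = 63, from 84.5% to 52.7%.

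**Step 4. The primary comparison, G2 versus G0.** Two-sample t, two-sided 0.05, 19 per arm, p = 0.70, r = 0.5. The non-centrality is d·√(n/2).

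- Full effect: 0.848 × √9.5 = 2.61, power 72.0%.
- Diluted, mean shift only: d = 0.848 × 0.85 = 0.721, non-centrality 2.22, power 58.0%.
- Diluted, with the extra G2 variance from mixing the two kinds of women: added variance 0.7 × 0.3 × 1.475² = 0.457; G2 SD = √(3.48² + 0.457) = 3.545; pooled SD 3.513; d = 2.51 / 3.513 = 0.714; power 57.2%.

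Steps 2 and 3 ignore this mixture variance. Including it would lower those powers slightly further.

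**The case against.** The strongest reply is that the size of the loss is not in the plan. A reader might infer that the plan's own basis implies about 48% power. It does not: that figure needs 30% of women to be non-adherent and every one of them to gain nothing, and the documents state neither. Zero benefit is also the extreme case, short of harm. A woman who attends 21 of 32 sessions (66%) counts as non-adherent but has had most of the programme. This objection stands, and it is why the result is given as a range.

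A reader might also take the 70% threshold as a forecast that 70% of women will adhere. It is a criterion applied to each woman and says nothing about how many will meet it. Likewise, the remark about a large majority missing it is a trigger for a sensitivity analysis, not a prediction.

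Three further points have weight. The reference effect may already reflect imperfect attendance in its source; the documents do not say, and if so the additional loss is smaller. Many trials are sized on an assumed ITT effect with no separate adherence allowance, so the lack of one is not in itself an error. And the dose–response analysis, the optional per-protocol analysis and the 95% confidence intervals would make low attendance and imprecision visible beside a null result, so a misreading is possible rather than certain.

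None of this rescues the sentence. The secondary analyses do not restore power to the ITT comparison. Whatever adherence the 2.95 points reflects, worse adherence that reduces the mean effect lowers power below the planned figure.

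**Conclusion.** The statement that ITT analysis keeps the primary analysis fully powered under substantial non-adherence is wrong as written. Section 2.4 makes no allowance for dilution that could support it.

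The size is conditional. With 30% of women non-adherent, only G2 differing, f = 0.40 and 63 analysed, omnibus power falls from about 80% to between 48% (no benefit in non-adherers) and 73% (three quarters of the effect). With f = 0.424 and no benefit, it falls from 80% to 48% at N = 57, or from 84.5% to 53% at N = 63. For G2 versus G0 with 19 per arm and half the effect in non-adherers, it falls from 72% to about 57–58%.

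A reader might go further and conclude that ITT is the wrong primary analysis or that the trial must be enlarged. The documents do not support that: ITT is sound for the comparison of allocated packages, and no expected adherence is given from which a new sample size could be set. Because the analysis set, model, multiplicity rule and sample size are all untouched, this is a should-fix correction of wording.

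**What to change.** 1. In Section 3.9, delete the clause that contains "ensuring that the primary effectiveness analysis remains fully powered even if a significant proportion of participants fail to meet compliance thresholds", from the word before it to the end of that sentence. The definition of the ITT population stands without it.
2. In Section 2.4, state that the power figure assumes the planned mean effect across all randomized G2 women, and that the 10% inflation covers missing T1 data only.
3. In the same place, state that power falls if non-adherence dilutes the mean effect, and give the range above with its assumptions: adherent share, effect kept by non-adherers, f and N.

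The cost is a few sentences in two sections and a less favourable account of power. ITT remains the primary analysis; no patients, visits or procedures are added.

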### 2.6. Intervention

#### 2.6.1. Health Education Programme G0 (Control Group)

Participants assigned to the control group (G0) will receive a standardized informational leaflet focused on evidence-based lifestyle modifications. This material will outline comprehensive instructions and recommendations for maintaining an active lifestyle, promoting self-care, and fostering healthy habits.

The content will be aligned with World Health Organization recommendations on risk reduction in cognitive decline and dementia [29]. The key areas covered in the intervention include:Nutritional optimization: Adoption of a balanced and nutritious diet.Physical & Mental Activity: Regular exercise and engagement in cognitively stimulating tasks.Psychosocial Factors: Maintenance of robust social connections and effective stress management techniques.Sleep Hygiene: Strategies for ensuring restorative and adequate sleep.Metabolic & Toxic Habits: Proper hydration, smoking cessation, and the avoidance of excessive alcohol consumption.

Strictly following the study design, this group will not receive cognitive individual or group stimulation. This group serves as a baseline comparison to evaluate the natural progression of cognitive symptoms under standard care and general health recommendations.

To capture the true, unaltered natural progression of neurocognitive symptoms under standard oncological care, the G0 group follows a passive, no-contact design between evaluations. While this limits real-time behavioral tracking, it deliberately prevents the introduction of reactive biases or artificial behavioral modifications often triggered by frequent researcher contact (the Hawthorne effect). Nonetheless, any spontaneous or clinically significant changes in participants’ lifestyle, sleep hygiene, or psychological status during this period will be captured and quantified via the multi-domain secondary psychometric outcomes (such as the PSQI and Hamilton scales) administered during the post-intervention assessment (T1).

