#### 2.6.2. Cognitive Training Group (CT) G1

Participants in the Cognitive Training (CT) group (G1) will undergo a structured programme focused on everyday cognition, administered individually to each patient. The intervention will be delivered through a meticulously developed dossier designed specifically for the objectives of this study. Notably, all participants in this arm will receive identical tasks, with no individualized adaptations for difficulty level or functional profile.

The intervention is structured into four consecutive one-month training periods (P1–P4), totaling 80 activities (20 activities per period). Participants are required to complete five activities per week. To monitor treatment adherence and ensure compliance with therapeutic guidelines, a dual follow-up system will be implemented:Remote Follow-up: Conducted via video call at the conclusion of P1 and P3 (Months 1 and 3).In-person Follow-up: Conducted at the clinic at the conclusion of P2 and P4 (Months 2 and 4) to evaluate progress and address emergent concerns.

The final evaluation for G1 will coincide with the completion of the fourth training period (P4). This group serves to control the effects of cognitive stimulation and professional monitoring without the specific multimodal components of the ALMA.

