#### 2.6.3. ALMA Group Intervention G2

The ALMA intervention is designed as a cognitive intervention programme tailored specifically for breast cancer patients. The primary objective is to address the effects of commonly known chemobrain by targeting cognitive domains commonly affected in CRCI. Beyond cognitive recovery, the programme aims to support self-esteem and patient empowerment through personalized and ecologically valid activities.

The intervention will be delivered through face-to-face group sessions at the Faculty of Psychology of the University of Salamanca. Each ALMA group will include up to six participants. If more than six participants are allocated to G2, additional groups will be created and delivered using the same intervention manual, session structure, materials, and monitoring procedures.

Group size will be limited to six participants to facilitate interaction, individualized support, and consistency in intervention delivery. The programme will span four months, with two 120 min sessions per week, resulting in a total of 32 sessions. The ALMA intervention is characterized by the following components:Targeted Cognitive Stimulation: Structured exercises focusing on memory, executive functions, attention, language, and mathematical/logical reasoning with dynamic adjustments to address specific patient deficiencies.Neuro-education & Health Literacy: Integrative discussions on neuroscience, cognitive health, and overall well-being to foster self-management.Group Dynamics: A collaborative environment designed to facilitate social support and emotional resilience among peers.

The activities will be adaptively tailored to the participants’ functional profiles, ensuring that the stimulation is both accessible and clinically relevant.

To ensure the replicability of the ALMA intervention, the operational components, session structure, materials, and monitoring procedures will be standardized and described in detail in Supplementary Material S1.

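### If women in the same ALMA group change alike, the participant-only random intercept understates the standard errors of both primary contrasts

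*Protocol article*

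**What the plan says.** Section 2.6.3 of the protocol article describes face-to-face ALMA sessions: "Each ALMA group will include up to six participants". It adds: "If more than six participants are allocated to G2, additional groups will be created". Group interaction is a listed component of the treatment: "A collaborative environment designed to facilitate social support and emotional resilience among peers". Section 2.4 plans the trial "with 21 participants allocated to each of the three study arms".

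The other two arms have no such grouping. G1 is "administered individually to each patient" (section 2.6.2), and "the G0 group follows a passive, no-contact design between evaluations" (section 2.6.1).

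For the primary outcome, section 3.9 sets out a linear mixed model with arm, visit and their interaction as fixed effects, and "a parsimonious random-effects structure restricted to a random intercept for each participant", meant to handle the correlation between a woman's two visits, with random slopes left out. Secondary outcomes use the same framework. The two planned primary comparisons, G2–G0 and G2–G1, are Holm-corrected. The article mentions no ALMA-group term, robust variance, ICC, design effect or sensitivity analysis for clustering.

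**The concern.** This is a partially nested design: one arm is clustered and two are not. Women in one ALMA group share 32 sessions of 120 minutes, with joint discussion and feedback. Section 4.1 says that group-based support may contribute to cognitive functioning, among other things. On the protocol's own reasoning, changes within a group may therefore be correlated.

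The model treats the 21 G2 women as independent. Both confirmatory contrasts use the same G2 mean, so a chance group-level fluctuation moves both in the same direction, and Holm's procedure does not repair a wrong standard error. At stake are the coverage of the intervals and the error rate of the primary claim.

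This is not a detail left to a later analysis plan, because the article fixes the random-effects structure and limits it to the participant.

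**Working it through.** **The plan's own figure.** The plan gives no figure for clustering. Its sample size of 57 comes from a one-way ANOVA on independent observations, with no design effect. An exact noncentral-F calculation gives 57 (power 80.2%) at the unrounded f = d/2 = (2.95/3.48)/2 = 0.424. At the stated f = 0.40 it needs 66. That mismatch is a separate matter and does not affect this point.

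**Inputs.** From the article: 21 women per arm, at most six per ALMA group, a difference of 2.95, SD 3.48, two-sided tests, Holm over two contrasts. Assumed: ICC of change 0.02 to 0.20, total variance of change equal in all arms, complete data.

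**Number of groups.** 21/6 = 3.5, so at least four. The fullest near-even split is 6/5/5/5.

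**Why the participant intercept does not help.** It enters both visits equally and subtracts out of T1 − T0. A shared group effect on change stays in the residual, which the model takes as independent. With complete data, the interaction test is the pooled-variance comparison of change scores on 63 − 3 = 60 degrees of freedom.

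**Formulas.** Let m̃ = Σm²/Σm, taken over the ALMA group sizes m.
- Design effect in G2: DE = 1 + (m̃ − 1) × ICC.
- True SE / modelled SE for G2 against an unclustered arm of 21: √((1 + DE)/2).

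For 6/5/5/5, m̃ = (36 + 25 + 25 + 25)/21 = 111/21 = 5.29. For seven groups of three, m̃ = 3. Example at ICC 0.10 with 6/5/5/5: DE = 1 + 4.286 × 0.10 = 1.429, and √(2.429/2) = 1.10.

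Test size and Holm family-wise error come from simulated change scores, with up to 100,000 trials per setting. Repeat runs differ by up to about 0.3 percentage points.

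| ICC | DE, 6/5/5/5 | SE excess | Size of 5% test | Holm family-wise error | SE excess, 7 × 3 | Size of 5% test, 7 × 3 |
|---|---|---|---|---|---|---|
| 0.02 | 1.09 | 2% | 5.5% | 5.1% | 1% | 5.0–5.2% |
| 0.05 | 1.21 | 5% | 6.2% | 6.0% | 2.5% | 5.6% |
| 0.10 | 1.43 | 10% | 7.5% | 7.4% | 5% | 6.2% |
| 0.20 | 1.86 | 20% | 10% | 10.3% | 9.5% | 7.3% |

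At ICC 0 the simulated size is 5.0% and the Holm family-wise error 4.6%.

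**Power with a correct standard error.** SE = 3.48 × √((1 + DE)/21). At ICC 0 this is 1.074, and power is Φ(2.95/1.074 − 1.96) = 78%. For groups of 6/5/5/5 at ICC 0.05, 0.10 and 0.20 it falls to 74%, 70% and 63% (normal approximation, 21 per arm, two-sided 5%).

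**The case against.** A reader might infer that the standard errors are certainly too small and the type I error certainly inflated. The documents do not support that: the harm requires a positive ICC of change in MoCA, and they give none. They also offer reasons for a modest value:
- One professional delivers ALMA (sections 2.11 and 6), so there is no variation between therapists.
- Section 3.8 holds the session structure constant.
- Tasks are adapted to individual profiles.
- MoCA is an individually administered performance test, while the peer component in section 2.6.3 is aimed at social support and resilience.

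These points stand as reasons for caution about size. Nothing in the article supports an ICC as high as 0.20. They do not justify zero either, given what section 4.1 says about cognitive functioning.

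Four groups is also a minimum. With 21 allocations to G2 over 12 months (1.75 a month), a group of six takes 6/1.75 = 3.4 months to fill, so more and smaller groups are plausible. The seven-group columns show roughly half the SE excess.

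Holm's procedure is slightly conservative here, so family-wise error is barely above 5% at ICC 0.02 with four groups. That also stands.

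A second tempting inference is that a partially nested model must become the primary analysis. That is debatable, because about four groups estimate a between-group variance poorly. If the G2 variance rests on 3 degrees of freedom and the unclustered arms' variance on 40, Satterthwaite gives about 2²/(1/3 + 1/40) = 11 degrees of freedom at equal variances, against 60. The critical value alone then rises by about 10% at the 5% level and 13% at the 2.5% Holm step.

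**Conclusion.** The concern holds conditionally. The stated model makes no allowance for ALMA-group clustering, and its wording rules one out, in both Holm-tested contrasts. If the within-group ICC of change is above zero, their standard errors are too small.

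The size depends on the ICC and on how the groups form. At ICC 0.02 the effect is negligible. At 0.05 it is small: SE about 2.5% to 5% too low, and a 5% test of size about 5.6% to 6.2%. With four groups it becomes material from about 0.10, where Holm family-wise error is about 7.4%. These figures assume complete data, equal total variance across arms and the two group layouts shown. The change should be made, but the documents do not show that the primary result would be invalid.

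**What to change.** 1. Record each G2 participant's ALMA group number prospectively.
2. In section 3.9, remove the wording that limits random effects to the participant.
3. Prespecify, before data are seen, that both primary contrasts are also reported with the G2 variance inflated for the actual group sizes at fixed ICCs of 0.02, 0.05 and 0.10. That is, replace s²(1/n₂ + 1/n_c) with s²(DE/n₂ + 1/n_c), where n₂ is the number in G2 and n_c the number in the comparator arm.
4. State that a significance claim will be qualified if it does not survive these adjustments.
5. Optionally, add a partially nested model as a further sensitivity analysis: a group effect on change in G2 only, with Satterthwaite or Kenward–Roger degrees of freedom. The effect must act on change, because a group intercept common to both visits would cancel just as the participant intercept does.

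The cost is one recorded variable and a few sentences, plus wider intervals and lower power in the adjusted analyses. Under the optional model the intervals would be markedly wider, because about four groups leave few degrees of freedom.
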